## **1. Background and Objectives**

Intracerebral hemorrhage (ICH) is one of the major stroke subtypes leading to severe disability and mortality. After the acute phase, patients often experience significant lower limb motor dysfunction, manifesting as muscle weakness, abnormal muscle tone, impaired coordination and motor control, and balance deficits. These functional impairments not only severely affect the patient's ability to walk independently and increase the risk of falls but also greatly limit their participation in daily activities and social functions, resulting in a marked decline in overall quality of life.

Currently, the recovery of motor function after ICH depends on the remodeling and compensation of the central nervous system. Promoting neuroplasticity has become a core goal of rehabilitation therapy. Repetitive Facilitative Exercise (RFE) is a rehabilitation technique that combines task-oriented repetitive movements with specific sensory input. It aims to reinforce correct movement patterns and reconstruct neural control pathways between the brain and limbs through high-intensity, repetitive functional task training supplemented by manual or instrumental facilitation of relevant muscle groups and nerves. Existing research suggests its potential in improving limb function after stroke.

On the other hand, non-invasive neuromodulation techniques offer new avenues for stroke rehabilitation. Transcutaneous Auricular Vagus Nerve Stimulation (taVNS) activates the vagus nerve pathway non-invasively by stimulating the auricular area where the vagus nerve distributes. This technique is believed to modulate the release of neurotransmitters (such as norepinephrine) in the brain, enhance levels of neurotrophic factors, and potentially optimize the microenvironment for neural repair by regulating neuroinflammation and cerebral blood flow, thereby promoting functional reorganization of the motor cortex and networks from the "central" side.

Theoretically, combining Repetitive Facilitative Exercise, which focuses on "peripheral facilitation" and "task repetition," with Transcutaneous Auricular Vagus Nerve

Stimulation, which focuses on "central modulation" and "neuroplasticity regulation," may produce synergistic effects. This combined intervention strategy is expected to simultaneously address both peripheral sensory input and central neuromodulation, promoting a more comprehensive recovery of lower limb motor function after ICH. However, there is a lack of high-quality clinical evidence regarding the combined application model and definitive efficacy of these two innovative techniques.

Therefore, this study aims to systematically evaluate the effects of Transcutaneous Auricular Vagus Nerve Stimulation combined with Repetitive Facilitative Exercise on lower limb motor function, walking ability, and gait parameters in patients during the recovery phase of ICH through a randomized controlled trial. The goal is to provide a new, evidence-based multimodal combined intervention strategy for ICH rehabilitation.

## **2. Research Methods**

### **2.1 Study Design**

This is a single-center, assessor-blinded, randomized controlled trial. Eligible patients will be randomly assigned to either the Combined Intervention Group (receiving real taVNS combined with RFE) or the Control Intervention Group (receiving sham taVNS combined with RFE). Both groups will receive consistent basic pharmacological treatment and other conventional rehabilitation therapies.

In this study, allocation concealment was implemented using the sealed envelope method. An independent statistician generated the randomization sequence by computer and placed the allocation results into sequentially numbered, opaque, sealed envelopes, which were then kept by a third party. When participants were enrolled, researchers opened the envelopes in sequential order to obtain the allocation results.

### **2.2 Study Participants**

**2.2.1 Sample Size Estimation:** Based on preliminary trial results, using the sample size calculation formula for comparing means between two independent samples, with the primary outcome measure (FMA-LE score) expected effect size  $d=0.8$ ,  $\alpha=0.05$

(two-tailed), and power  $1-\beta=0.8$ , an estimated 26 participants per group is required. Considering an approximate 10% dropout rate, 29 participants per group are planned, totaling 58 participants.

#### 2.2.2 Inclusion Criteria:

1. Diagnosis of supratentorial ICH confirmed by CT or MRI, with stable vital signs and neurological function;
2. Disease duration of 1-6 months (recovery phase);
3. Age 18-75 years;
4. Presence of unilateral lower limb motor dysfunction (Brunnstrom stage of the affected lower limb  $\geq$  III);
5. Ability to walk short distances with minimal assistance or supervision (Functional Ambulation Classification  $\geq$  level 2);
6. Clear consciousness, able to understand and cooperate with assessments and treatments;
7. Signed informed consent from the patient or their legal guardian.

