### 2.4.1 Primary Outcome Measure:

1. Lower Limb Motor Function: Assessed using the Fugl-Meyer Assessment for Lower Extremities.

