## 2.6 Statistical Analysis Methods

Data analysis will be performed using SPSS software. Continuous data conforming to a normal distribution will be presented as mean  $\pm$  standard deviation and compared between groups using independent samples t-tests; within-group comparisons (pre- vs post-intervention) will use paired samples t-tests. Continuous data not conforming to a normal distribution will be presented as median (interquartile range) and analyzed using non-parametric tests. Categorical data will be analyzed using chi-square tests. All statistical tests will be two-sided, with a P-value  $< 0.05$  considered statistically significant.

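### Section 2.6 compares the arms without adjustment although baseline FMA-LE and time since haemorrhage are both known for every patient; a model with both would recover precision, most of it from the baseline score

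*Protocol*

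**What the plan says.** - **Eligibility (Protocol 2.2.2):** "Disease duration of 1-6 months (recovery phase"). Time since haemorrhage must therefore be known before a patient can enter.
- **Primary outcome (2.4.1):** lower limb motor function, "Assessed using the Fugl-Meyer Assessment for Lower Extremities". Section 2.4 schedules assessments before treatment and straight after the 6 weeks, so a baseline score also exists.
- **Allocation (2.1):** "An independent statistician generated the randomization sequence by computer", held in sealed envelopes. No stratification or minimisation is stated.
- **Analysis (2.6):** normally distributed outcomes are "compared between groups using independent samples t-tests"; "within-group comparisons (pre- vs post-intervention) will use paired samples t-tests"; other continuous data are "presented as median (interquartile range) and analyzed using non-parametric tests". No covariate and no regression model is named.
- **Sample size (2.2.1):** d = 0.8 on FMA-LE, two-tailed alpha 0.05 and power 0.8, from which "an estimated 26 participants per group is required"; 29 per group, 58 in total, after about 10% dropout.

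**The concern.** The trial looks for a gain over 6 weeks in patients whose own recovery may still be under way. Two values known at entry plausibly bear on the 6-week score. The baseline FMA-LE shows where a patient starts. Time since haemorrhage bears on how much recovery may still be to come, and two patients with the same baseline score can stand at 1 month and at 6 months. The stated comparison between arms uses neither. The paired tests use baseline, but only within an arm, so they do nothing for the contrast between arms.

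At stake is precision. Variation that the model could explain stays in the error term, and in a trial of 58 a chance difference between arms in starting level or recovery stage passes straight into the estimate.

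**Working it through.** **Inputs from the protocol.** d = 0.8, two-sided alpha 0.05, power 0.8, 26 evaluable per arm, 29 per arm randomised (2.2.1); onset window 1 to 6 months (2.2.2).

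**Assumptions, not in the documents.** Onset times uniform over the window; correlation ρ of baseline with 6-week FMA-LE of 0.5, 0.6 or 0.7; correlation r of onset time with the outcome of 0.1 to 0.4; d = 0.8 scaled to the SD of the 6-week score.

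**1. The plan's figure.** The exact two-sample t calculation gives 25.52, so 26 per arm, with power 80.7%. Then 26/0.9 = 28.9, so 29 per arm and 58 in total. The stated sample size reproduces.

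**2. Chance imbalance in onset time.**
- SD of a uniform variable over 1 to 6 months: 5/√12 = 1.443 months.
- SE of the difference in means at 29 per arm: 1.443 × √(2/29) = 0.379 month.
- P(|difference| ≥ 0.5 month) = 2 × [1 − Φ(0.5/0.379)] = 0.187, about 19%. At 26 per arm the SE is 0.400 and the probability 21%.

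**3. What a 0.5-month gap does to the unadjusted estimate.** Shift = r × 0.5/1.443 = 0.346 r, in outcome SD.
- r = 0.3: 0.10 SD. r = 0.4: 0.14 SD. These are 13% and 17% of d = 0.8.
- If r is a partial correlation after baseline, and onset time is taken as unrelated to the baseline score, multiply by √(1 − ρ²) = 0.866, 0.800 or 0.714. The range becomes 0.07 SD (0.104 × 0.714) to 0.12 SD (0.139 × 0.866).

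**4. Power at 26 per arm.** With k covariates the residual variance is multiplied by (1 − ρ²)(1 − r²), the degrees of freedom are 50 − k, and estimating the covariates inflates the variance of the arm effect by an expected 1 + k/(49 − k). The noncentrality is

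0.8 × √(26/2) ÷ √[(1 − ρ²)(1 − r²)] ÷ √[1 + k/(49 − k)].

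Unadjusted it is 0.8 × √13 = 2.884, giving 80.7%. With baseline at ρ = 0.5 it is 2.884/√0.75 × √(48/49) = 3.30, giving 89.8%.

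| Model | ρ = 0.5 | ρ = 0.6 | ρ = 0.7 |
|---|---|---|---|
| Baseline only | 89.8% | 93.8% | 97.5% |
| + onset time, partial r = 0.1 | 89.5% | 93.5% | 97.3% |
| + onset time, partial r = 0.2 | 90.4% | 94.2% | 97.7% |
| + onset time, partial r = 0.3 | 91.8% | 95.2% | 98.2% |
| + onset time, partial r = 0.4 | 93.7% | 96.5% | 98.8% |

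From the unrounded values, onset time adds 0.2 to 0.5 points at r = 0.2, 0.7 to 2.0 at 0.3 and 1.3 to 3.8 at 0.4. At r = 0.1 it costs under half a point.

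**5. Onset time alone, without baseline.** The same formula with k = 1 gives 80.3%, 81.5%, 83.5% and 86.3% at r = 0.1, 0.2, 0.3 and 0.4, against 80.7% unadjusted.

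**The case against.** The case against runs as follows. A two-sample t-test after randomisation is unbiased with correct type I error, and it matches the method behind the sample size, so nothing in the protocol is wrong. Covariates are often left to a statistical analysis plan, which may exist unseen. The correlation that drives any benefit from onset time is not in the documents, and once baseline is in the model that benefit is small.

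Most of this stands. A reader might infer that the test is biased or that the trial is too small; the protocol supports neither, since allocation is random and 26, 29 and 58 reproduce. A reader might also credit onset time with the whole rise over the unadjusted test. Step 5 shows that even this gain is modest, and the model worth using also contains baseline, against which onset time adds only the few points in step 4. Nor does missing stratification make the comparison invalid, and adjustment does not require it.

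What does not stand is the view that there is nothing to change. Section 2.6 does not leave the method open: it names an unadjusted test, so an analysis plan that added covariates would depart from the protocol.

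**Conclusion.** The point holds as one about efficiency. The stated test is valid but ignores two values known for every patient, and so leaves precision unused and chance imbalance uncorrected. Most of the gain comes from baseline FMA-LE: from 80.7% to about 90% or more if its correlation with the 6-week score is at least 0.5. Time since haemorrhage is a useful but minor addition: 2.0 points at most at a partial correlation of 0.3, 3.8 at most at 0.4, and a slight loss at 0.1. Its further value is that an imbalance in recovery stage, if one arises, is dealt with by a rule fixed beforehand.

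All the correlations and the uniform onset times are assumptions. Section 2.6 also does not say whether the t-test is applied to 6-week scores or to changes. If to changes, part of the baseline gain is already taken: with equal variances at the two visits, the baseline-adjusted residual variance is (1 + ρ)/2 of the change-score variance, or 0.75 to 0.85 for ρ from 0.5 to 0.7. Severity: minor.

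**What to change.** In section 2.6, state that the primary comparison is a linear model of 6-week FMA-LE on arm, baseline FMA-LE and time since haemorrhage as a continuous variable, and that the adjusted difference between arms is reported with its 95% CI. Fix this before unblinding, because a covariate added after an imbalance has been seen would look data-driven. The unadjusted t-test can stay as a supporting analysis.

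The cost is one sentence and two residual degrees of freedom against the t-test (48 instead of 50 at 26 per arm). No new data, visits, strata or patients are needed, and the sample size need not change.

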#### 2.2.3 Exclusion Criteria:

1. Brainstem or cerebellar hemorrhage, or cerebrovascular diseases requiring surgical intervention;
2. Comorbid severe dysfunction of vital organs (e.g., heart, liver, kidneys) or systemic infections and other serious complications;
3. Orthopedic conditions affecting lower limb function (e.g., unhealed fractures, severe arthritis) or peripheral neuropathy;
4. Local skin lesions, infections, or eczema in the auricle, unsuitable for auricular electrical stimulation;
5. Implanted electronic medical devices such as cardiac pacemakers, defibrillators, deep brain stimulators, or cochlear implants;
6. History of epilepsy, psychiatric disorders, or severe cognitive impairment (MMSE

score < 21), unable to cooperate with the study;

7. Known or suspected allergy to electrode adhesive;

8. Concurrent participation in other clinical trials that may interfere with the results of this study.

### 2.3 Intervention Protocol

All interventions will be performed by uniformly trained therapists.

Combined Intervention Group: Receives Transcutaneous Auricular Vagus Nerve Stimulation synchronized with Repetitive Facilitative Exercise.

Control Intervention Group: Receives sham Transcutaneous Auricular Vagus Nerve Stimulation synchronized with Repetitive Facilitative Exercise.

The intervention frequency for both groups is 5 days per week for 6 weeks.

#### 2.3.1 Repetitive Facilitative Exercise Protocol:

Therapists will select and perform facilitative exercises targeting key lower limb muscle groups and movement patterns based on the patient's functional level. The training will follow a standardized operational procedure, including:

1. Facilitation Induction Using specific techniques such as brushing, tapping, or vibration to stimulate target muscle groups or dermatomes to enhance their excitability.

2. Assisted Active Movement: Immediately after facilitation, the therapist assists the patient in attempting active movement of the target action, such as flexion/extension, adduction/abduction of the hip, knee, and ankle.

3. Repetitive Task Training: Integrating the elicited movements into functional tasks for high-repetition practice (e.g., 30-50 repetitions per set, multiple sets daily), such as bridging in supine, sit-to-stand transfers, weight shifting, and stepping exercises.

The training emphasizes movement quality, intention, and repetition, with gradual progression in difficulty and reduction of assistance based on patient improvement.

#### 2.3.2 Transcutaneous Auricular Vagus Nerve Stimulation Protocol

Device and Parameters: A Transcutaneous Auricular Vagus Nerve Stimulator will be used.

Real stimulation parameters are set as: frequency 25Hz, pulse width 250-500 $\mu$ s, using an intermittent stimulation mode (e.g., 30 seconds on, 30 seconds off). Intensity is adjusted to a level where the patient feels a distinct but non-painful tingling sensation (typically 2-3mA below the perception threshold).

Stimulation Site: Electrodes are attached to the left concha area (distribution area of the auricular branch of the vagus nerve).

Sham Stimulation Setup: The device appearance, electrode placement location, and operational procedure are identical to the real stimulation group. However, the stimulator delivers an ineffective, very low-intensity current that is barely perceptible (e.g., <0.1mA) to mimic device operation.

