### 3.4 Adverse Event Reporting

#### 3.4.1 Adverse Events

Adverse events include: ① Skin tingling sensation in the electrical stimulation area: The patient's experience will be recorded, along with their tolerance level. Generally, the tingling sensation gradually diminishes or disappears after stimulation. If the patient cannot tolerate it, they will withdraw from the experiment. ② Fatigue: Fatigue may occur during exercise therapy or functional assessments. Subjects will be given timely rest, and fatigue levels will be recorded. Fatigue typically alleviates after rest. Throughout the experiment, dedicated medical staff will accompany the patient to ensure their safety as much as possible.

3.4.2 Definition of Adverse Events: Harmful reactions unrelated to the experimental objectives that occur during the normal intervention process.

3.4.3 Severity Assessment: Adverse reactions are categorized into levels 1–5 based on severity:

- Level 1: Mild; asymptomatic or extremely mild symptoms; detectable only through tests; no intervention required.
- Level 2: Moderate; requires minor or non-invasive local intervention; decline in instrumental activities of daily living scale scores.
- Level 3: Severe or clinically significant but not immediately life-threatening; requires hospitalization or extended hospital stay; disability; decline in physical self-care ability

scale scores.

- Level 4: Life-threatening; requires urgent intervention.

- Level 5: Death due to adverse reaction.

3.4.4 Correlation Judgment: Harmful reactions unrelated to the experimental objectives that occur during the experiment, such as skin tingling during electrical stimulation, fatigue during exercise training or functional assessments, or falls, are considered adverse reactions related to this experiment.

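### Section 2.3.2 contradicts itself on active-arm intensity: the current must be clearly felt, yet is placed 2-3 mA below the perception threshold

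*Protocol*

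**What the plan says.** Section 2.3.2 of the Protocol gives the active settings one by one. Frequency and pulse width come first: "Real stimulation parameters are set as: frequency 25Hz, pulse width 250-500" microseconds. The duty cycle follows: "using an intermittent stimulation mode (e.g., 30 seconds on, 30 seconds off". Section 2.3 gives the schedule: "The intervention frequency for both groups is 5 days per week for 6 weeks". None of these is in question.

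Intensity is then set by titration: "Intensity is adjusted to a level where the patient feels a distinct but non-painful tingling sensation (typically 2-3mA below the perception threshold". That bracket holds the only mA figure given for active stimulation. The only other mA figure in the document is the sham example of less than 0.1 mA. Of the sham, section 2.3.2 says that "the stimulator delivers an ineffective, very low-intensity current that is barely perceptible".

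Two other places bear on the reading. Section 3.4.1 lists tingling where the current is applied among the adverse events and adds: "Generally, the tingling sensation gradually diminishes or disappears after stimulation". Section 2.1 says of the background care: "Both groups will receive consistent basic pharmacological treatment and other conventional rehabilitation therapies".

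**The concern.** A perception threshold is the lowest current that a person can feel. The main clause tells the therapist to reach a current that the patient clearly feels. The bracket says that this same current usually lies below the point at which anything is felt.

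The sentence matters because of where it sits. Both arms receive RFE on the same schedule with the same background care, so real versus sham stimulation is the only planned difference. Section 2.3.2 also makes the device's appearance, the electrode position and the procedure the same in both arms, which leaves the current delivered to separate real from sham. A therapist who worked from the bracket would give an unfelt current in the active arm, no more perceptible than a sham described as just perceptible. The sentence as written also cannot serve as the standard for judging a deviation under section 3.2, or for repeating the dose elsewhere.

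**Working it through.** **Inputs**, all from section 2.3.2: the sensation clause, and the bracket of 2-3 mA below the perception threshold. Let T be a patient's perception threshold and I the active current, both in mA. The protocol gives no value of T.

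**Step 1: what each half requires.**
- Sensation clause (felt): I ≥ T.
- Bracket: T − 3 ≤ I ≤ T − 2.

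**Step 2: can both hold?** The largest current that the bracket allows is T − 2, which is less than T for every T. The ranges never overlap, so the stated figure cannot be reconciled with the rule that it is meant to illustrate.

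**Step 3: can the bracket be delivered at all?** Amplitude cannot be negative. The values of T below are illustrative only.

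| T (mA) | Bracket: T − 3 to T − 2 (mA) | Deliverable? | Felt? |
|---|---|---|---|
| 0.5 | −2.5 to −1.5 | no | no |
| 1 | −2 to −1 | no | no |
| 2 | −1 to 0 | only as zero current | no |
| 3 | 0 to 1 | yes, from zero upward | no |
| 4 | 1 to 2 | yes | no |
| 5 | 2 to 3 | yes | no |

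For T below 2 mA no current satisfies the bracket. For T from 2 to just under 3 mA only part of it can be delivered. The whole bracket is available only from T = 3 mA upward, and even there every value is below threshold.

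**Step 4: which half was probably intended?** Three features favour the sensation clause.
- It is the instruction itself, and the bracket only comments on it.
- Section 3.4.1 expects tingling under the electrodes. The support is indirect, because that section neither sets an intensity nor names an arm.
- The sham is described as just perceptible, so an active current below threshold would be no easier to feel than sham. This uses the description only and does not treat the sham's example figure as a threshold.

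None of these shows what the bracket was meant to say. It might be an absolute current, or an offset from another threshold such as pain, but the text does not decide between them.

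**The case against.** The strongest reply is that the sentence works despite the bracket. The main clause is a complete titration rule with a lower bound (felt) and an upper bound (not painful). The patient's own report would expose a setting that is too low. The bracket is softened by the word typically, and for a low threshold it cannot be carried out. Section 2.3 adds: "All interventions will be performed by uniformly trained therapists". Titration to sensation needs no fixed mA figure, so the lack of another amplitude is not a separate defect.

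Most of this stands, and it limits the practical risk. It does not remove the error. The word typically allows departures from a usual value, but here the usual value itself breaks the rule. Uniform training makes therapists alike without showing which half of the sentence they are taught.

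A reader might infer more than the document supports:
- **That the active dose is undefined.** It is not, because the sensation clause can be followed alone.
- **That the active dose is wrong by 2 to 3 mA for every patient.** Those figures only restate the bracket. For T below 2 mA the lowest deliverable current is zero, so the shortfall from threshold is at most T, which is less than 2 mA. A full 3 mA shortfall needs T of at least 3 mA, and no value of T is given.
- **That the sham figure fixes the threshold near 0.1 mA.** It is an example of a sham setting, not a measured threshold.
- **That power or the outcome is affected.** Nothing shows how often the bracket would be followed, and the sample size of 58 does not depend on this sentence.

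**Conclusion.** The inconsistency is real and the sentence is wrong as written: no current satisfies both halves, whatever the patient's threshold. This rests only on the ordinary meaning of a perception threshold and on amplitude not being negative. The further result, that the bracket cannot be delivered at all when the threshold is below 2 mA, rests on the same two premises.

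The size of any dose error cannot be derived from the document, and no loss of power or bias in the outcome is claimed. The severity is minor to moderate: a workable and probably intended rule stands beside the faulty figure, but the fault concerns the current that defines the contrast between the arms.

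**What to change.** Delete the bracket in section 2.3.2, or replace it so that a single rule remains, for example: above the perception threshold and below the pain threshold. The investigator should confirm the wording. If an mA figure is kept, the text should say whether it is an absolute current or an offset, and if an offset, from which named threshold. The therapist instructions should then be brought into line with the corrected sentence.

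The cost is an edit to one bracket plus the matching instructions. Sample size, outcomes, visits and analysis do not change.
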